### Intervention

All groups will receive usual WIC nutritional assessment and counseling benefits, including monthly nutritional counseling sessions based on a state-approved curriculum with trained nutritionists and peer counselors [34,35]. These sessions are designed to support each woman’s motivations for healthy diet in pregnancy and include education on healthy diets, portion sizes, minimizing SSB intake, cooking skills, and recipes. The intervention period will begin at study enrollment and continues until the end of pregnancy (termination or miscarriage) or infant birth.

The control group (arm 1) will receive usual WIC counseling, as described above, and food benefits loaded onto their Electronic Benefits Transfer (EBT) card to use in person at approved grocery stores. At completion of study participation, arm 1 participants will receive a 1-year prepaid subscription to a grocery delivery service of their choosing.

Participants in arm 2 (WIC counseling + food delivery) will choose WIC-approved foods from an online survey, which will be purchased and delivered to their home biweekly by the study team via a grocery delivery service at no cost to the participant. Fruit and vegetable options will be offered as well as whole grains (cereal, bread, pasta) and proteins (milk, egg, cheese) as listed in the WIC-approved foods booklet (Textbox 1) [36]. The quantities of food will follow the WIC-approved allocations for each month. Participants must text or call the study team to confirm they received the food. These deliveries are not meant to replace their normal grocery shopping or use of WIC benefits but rather to make healthy eating more convenient, and participants are not restricted in their use of WIC food benefits by participating in this program. These foods are in addition to the WIC benefits they already receive.

Example grocery delivery options.
**Vegetables**
Baby carrots, broccoli, bell peppers, cauliflower, radishes, snap peas, green peas, avocados, tomatoes, cucumbers, celery, mushrooms, spinach, corn.
**Fruits**
Apples, pears, oranges, clementines, grapes, bananas, nectarines, peaches, strawberries, blueberries, raspberries, blackberries, watermelon, pineapple.
**Proteins and grains**
Yogurt, cheese, milk, whole grain bread, whole grain buns, whole grain tortillas, brown rice, whole grain cereal, beans, lentils, peanut butter, eggs.
**Unsweetened beverages**
Seltzer water, unsweetened tea, Spindrift, sparkling tea, bottled water

Participants in arm 3 (WIC counseling + food plus unsweetened beverage delivery), the home delivery of healthy foods, as described above, will be supplemented with the inclusion of participant-selected unsweetened beverages, in quantities comparable to their current SSB intake (based on self-reported consumption). Unsweetened beverages are intended to replace current SSB consumption. Because SSBs contribute to a significant number of excess calories among youth, this group includes unsweetened beverage delivery to further promote healthy weight gain. The unsweetened beverage choices will include bottled water (flavored or unflavored), unsweetened seltzer water (flavored or unflavored), and unsweetened teas. Artificially sweetened beverages and SSBs will be excluded.

### Participant Retention

Our study is designed to be low burden, so participants only have to maintain minimal communication via text, phone call, or email to remain in the study. In addition, participants are incentivized with Amazon gift cards for various components of the study. Participants in all arms receive US $20 for completing the enrollment process, baseline survey, first diet recall, and medical record request form. Participants in all arms will receive US $20 for each additional diet survey completed on their own throughout the course of the study (up to 5 total). For each week participants use their study provided scale, they will receive US $1, and an additional US $10 is given for the end-of-study interview. Women in the intervention arms receive biweekly grocery deliveries during their pregnancy, while women in the control arm receive free access to 1 year of a grocery delivery service at the end of their pregnancy. The resulting maximum incentive for participation is US $160 for participants who enroll at 10 weeks’ gestation, complete all study questionnaires, and remain active for the remaining 7 months of their pregnancy.

### Data Collection

At baseline, interested and eligible participants will complete the consent process to participate and respond to baseline measures, described in detail below. In addition to the baseline surveys, participants will be asked to share weight, physical activity, and diet recall data at specified times throughout the study period. The complete list of outcomes, covariates, and timeline of assessments is shown in Table 1.

**Table 1 table1:** Study outcomes and covariates with timeline of data collection.

Measure			Data source		Time points
**Primary outcome**					
	Total and weekly weight gain in pregnancy: above, below, or within guidelines	Prepregnancy weight: self-report and medical record review Pregnancy weight gain: BodyTrace scale and medical record review		At enrollment, weekly during pregnancy	
**Secondary outcomes**					
	Diet quality: Healthy Eating Index score	Paired ASA24^a^ diet recall surveys		Twice at baseline, twice at second trimester, twice third trimester	
	Prenatal complications: gestational diabetes, hypertensive disorders; delivery complications: operative delivery, shoulder dystocia, postpartum hemorrhage; and birth weight: small/large for gestational age	Medical record review		Postpartum	
**Process measures**					
	Delivery of WIC^b^-approved food and unsweetened beverages	Online grocery delivery orders; requested monthly by participants		Biweekly deliveries	
	Experience with deliveries	Phone interview		Postpartum	
	Medical/WIC record release	SignNow e-signature		At enrollment	
**Confounders/modifiers**					
	Age, race, ethnicity, socioeconomic status, home environment, food insecurity	Demographic survey		At enrollment	
	Physical activity	Physical activity survey		Weekly during pregnancy	
	Food behaviors	Cooking frequency, fast-food frequency, cooking confidence, eating disorder examination		At enrollment, postpartum	
	Body shape preference	Pulvers body image instrument		At enrollment, postpartum	
	WIC nutrition visits and food benefits redeemed	WIC record review		Postpartum	

^a^ASA24: Automated Self-Administered 24-hour.

^b^WIC: Special Supplemental Nutrition Program for Women, Infants, and Children.

### Sociodemographic Data

All sociodemographic data will be collected upon enrollment online or by phone with the study team. These include date of birth (to calculate age), self-reported race and ethnicity, highest level of education, free/reduced lunch status while in school (a valid measure of socioeconomic status among youth) [37], full address including zip code (for grocery delivery and delivery of BodyTrace scale), home environment (validated Home Food Environment assessment [38,39], other individuals in household, access to transportation), and a validated two-question food insecurity screen for youth to determine baseline access to food [40,41]. Participants’ and household members’ food allergies and cultural/religious food preferences will also be collected upon enrollment.

### Weight and BMI

Prepregnancy weight and height will be obtained by self-report and verified by medical record review after birth to determine prepregnancy BMI and identify target weight gain zones. Weekly weight measurements during pregnancy will be measured via a BodyTrace scale and recorded automatically using cellular connectivity (no Wi-Fi or cellular plan required) [42]. The scale will be mailed to participants’ homes upon enrollment. The BodyTrace scale provides valid weight measures and has been used by several other large-scale weight interventions [43-45].

### Dietary Intake

Dietary intake will be measured with paired assessments using the Automated Self-Administered 24-hour (ASA24) dietary recall survey [46-48]. This process has been validated by comparison to in-person 24-hour recalls and has been used by other studies of pregnant youth with low income [49,50]. At enrollment, participants will complete their first recall over the phone with the study team. A second baseline ASA24 survey will then be completed, approximately 2 to 5 days after enrollment. Participants will complete four additional ASA24 surveys using the same paired system during the intervention period. Two will be completed in the second trimester and two in the third trimester. Study team members will be available, as needed, to assist participants in completing all ASA24 surveys. Paired responses will be combined and used to calculate a Healthy Eating Index (HEI) score for each time point: baseline, second trimester, and third trimester [46,51]. The output from the ASA24 includes additional data on fruit and vegetable servings as well as other macronutrient data.

### Physical Activity

The American College of Obstetricians and Gynecologists recommends an exercise program of moderate intensity exercise for at least 20 to 30 minutes per day on most or all days of the week for pregnant women [52]. To measure physical activity, we will use an adaptation of the Youth Risk Behavior Survey and National Youth Physical Activity and Nutrition Study survey item that has been validated with accelerometer data [53-56]. The survey will be sent weekly via SMS text message to assess the proportion of time youth meet the guidelines, as physical activity impacts weight gain in pregnancy.

### Body Size Preference

Participants will complete the validated Pulvers Body Image [57] scale at enrollment and during the phone interview after birth to assess their body size preferences. At baseline, participants will be asked to identify their prepregnancy body shape and ideal body shape from the 9 options included in the Pulvers scale. At follow-up, participants will be asked to identify their current (postpartum) body shape and ideal body shape. Participants’ preference in body size may impact their weight-related behaviors and provides critical context on whether they wish to be or stay bigger after pregnancy or try to return to their prepregnancy size [58].

### Food Behaviors

Participants will be prompted to complete questions adapted from the Eating Disorder Examination Questionnaire Short and Youth Eating Disorder Examination-Questionnaire at baseline and end of study to identify perceptions of loss of control of eating, binge eating, weight/shape overvaluation, and body dissatisfaction [59-61]. Additional questions drawn and adapted from the National Health and Nutrition Examination Survey focused on the frequency of home-cooked meals in the household and fast-food meals [62] will also be asked as well as participants’ confidence in cooking meals [63,64]. These questions will be assessed during the baseline and end-of-study survey assessments.

### Text Message Reminders

SMS text messages will be sent to participants in all arms using Textizen.com, a GovDelivery platform. Participants will receive 2 to 3 SMS text messages per week reminding them to confirm their delivery, place their order, step on their scale, and respond to physical activity questions. These SMS text messages will also prompt participants to share any updates they may have regarding their pregnancy, allowing participants an opportunity to report on infant birth, miscarriage, or any other outcomes. In addition, participants will be prompted via SMS text message to complete their diet recall surveys throughout their pregnancy.

### Medical Records Data

Medical records will be requested from participants’ prenatal and delivery care sites within a few weeks of delivery using the release forms completed at enrollment. Data collected will include all health care visits during pregnancy and up to 12 weeks postpartum, including prenatal visits (diagnoses and complications), nutrition visits (number and content of visits), emergency department visits, inpatient stays, WIC counseling visits (number and type: nutrition vs breastfeeding), quantity of WIC foods redeemed, laboratory results (1-hour glucose tolerance test, A1C, blood glucose levels, complete blood count, urine studies, liver/renal studies), vital signs (weight, height, blood pressure, pulse), medications prescribed, complications during prenatal care (gestational diabetes, hypertensive disorders), infant birth weight, and gestational age at delivery.

### End-of-Study Interview

A phone interview will be performed after each woman gives birth to collect qualitative insights into participants’ experience with grocery/beverage delivery; the impact of delivery on their diet; overall WIC experiences; and end-of-pregnancy body preference, self-reported weight gain, physical activity, any prenatal or childbirth complications, plans for breastfeeding, and food insecurity.

### Data Analysis

To understand the effect of grocery delivery on pregnancy weight gain, diet quality, and health outcomes, weight will be measured weekly, dietary quality will be assessed twice per trimester, and perinatal outcomes will be assessed at the end of the pregnancy. All analyses will follow the intention-to-treat principle. Prior to analysis, assessment of missing data will be completed and appropriately imputed using multiple imputation methods [65].

Our primary outcome is appropriate weight gain in pregnancy, which is based on prepregnancy BMI and includes weekly weight gain and total weight gain recommendations. Total weight gain at birth will be categorized as above, below, or within the Institute of Medicine guidelines [5,33]. Multinomial logistic regression analysis will be used to compare the likelihood of falling above, within, or below guidelines for total weight gain in pregnancy across arms after adjusting for potential confounders such as age, race, ethnicity, socioeconomic status, and household characteristics. Confounders will be identified through significant findings in bivariate analysis comparing the three groups and by consideration of variables based on prior scientific evidence. Summary statistics of key time-dependent measures and other non–time-dependent measures will also be included as covariates. Modification of the study arm effect by key variables will be investigated through interaction terms in the regression model.

The trajectory of weight gain behavior, using each week’s categorized weight gain (within guidelines vs not), will additionally be assessed as the outcome in a clustered logistic regression model fit using a generalized linear mixed model framework. The study arm is the primary between-participant factor, while time (week) is the main within-participant covariate. The interaction term between time and arm is also a factor of interest, as it will allow us to assess changes in weight gain behaviors over time between study arms. A random participant-level intercept will account for within-participant clustering, and a random slope for time will be investigated to account for additional between-participant variability. Additional covariates and effect modifiers included in these regression models will be chosen using the same methods as before.

Our secondary outcome is diet quality as measured by the HEI score based on two ASA24 measurements at baseline and in the second and third trimesters [51,66]. A comparison of overall HEI scores between study arms will be carried out using separate linear mixed models with calculated HEI scores from each trimester as the outcome. As before, the study arm will be the primary between-participant factor; time, as measured by trimester, the within-participant covariate; and the interaction between arm and time will be assessed to measure the difference in trimester effect between the arms. Random participant-level intercepts and slopes for time will assess the deviation from the overall average and account for any within-participant clustering. Models will be adjusted for additional confounders and covariates, determined as in prior models. Fruit and vegetable intake, as well as other macronutrient details, will also be evaluated.

Prenatal complications, delivery complications, and birth weight (small/large for gestational age) are also secondary outcomes that will be assessed. Comparison of the proportion of participants with complications between study arms will be analyzed using a logistic regression model in a manner analogous to the primary outcome of appropriate weight gain in pregnancy.

The end-of-study interview transcripts will be analyzed using standard qualitative techniques [67-69]. Two investigators will review all transcripts, create memos of major concepts present, and iteratively develop a codebook. Transcripts will be coded and major themes and conclusions determined by consensus. Themes identified from these transcripts will describe participants’ satisfaction or dissatisfaction with delivery, perceived impact of food delivery on their health and diet, and other challenges/barriers to healthy behaviors during pregnancy. The interviews will be used to provide context and narrative to inform findings from quantitative outcome data, and will be used in dissemination to tell the participants’ perspective regarding the impact of grocery delivery.

Finally, we will conduct a cost analysis focused on costs from the payer perspective during the pregnancy period. All costs will be adjusted to current dollars and will represent average cost per participant. Our analysis will estimate the costs of delivering the intervention, including cost of grocery delivery service, increased costs for WIC due to increased redemption of food benefits [70], print and online media advertisements to maximize uptake, costs to train WIC staff on new procedures, and increased WIC visit time to allow staff to educate beneficiaries. Medical records data will also be used to identify the number and type of all medical care used by participants during pregnancy, including prenatal care visits, specialist visits and consultations, emergency department visits, inpatient care, and delivery care. The average total health care costs per participant associated with each arm of the trial will be calculated using nationally representative health care expenditure data from the most recent Medical Expenditure Panel Survey [71]. Although medical records data from their usual sources of care may not include visits to urgent care and outside facilities, this will not likely introduce bias due to randomization to study arms.

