### Sample Size Determination

Based on nationally representative studies of weight gain in pregnancy [4], we anticipate 30%, 45%, and 60% of participants in arm 1 (control), arm 2 (WIC + food delivery), and arm 3 (WIC + food plus unsweetened beverage delivery), respectively, to gain weight within the Institute of Medicine guidelines [5,33]. The sample size was determined using methods for comparing independent proportions, and a conservative alpha value of .01 was set for significance to address the multiple testing of 3 comparisons. A sample size of 774 (258 per arm) after attrition will have over 80% power (2-tailed) to detect these differences as statistically significant. Accounting for an anticipated 10% attrition rate based on our preliminary study and low-burden design, we will aim to recruit 285 participants per study arm (855 total).

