### Randomization

Upon completion of baseline screening and assessments, 855 pregnant young women will be randomly assigned to either the control group or one of the two experimental groups. We will use county-level block randomization to assign participants in a 1:1:1 ratio to the three study arms. The treatment assignments will be created and stored in the Consulting for Statistics, Computing and Analytics Research randomization tool managed by the University of Michigan. No treatment assignments will be made until after collection of baseline data (consent, demographic survey, diet recalls, and other baseline questionnaires). At this time, the participant will be notified of their arm assignment and additional details required for grocery delivery (delivery address, day, and time) will be collected from participants in arms 2 and 3. All personnel who assess study outcomes are masked to group assignment. Participants and staff implementing the grocery delivery are not masked to group assignment.

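### One of the two stated routes to the covariate set is significance testing between randomised arms, which says nothing about prognosis and leaves the adjusted primary model dependent on data seen by arm

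*Protocol article*

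**What the plan says.** The Randomization section of the protocol article states: "We will use county-level block randomization to assign participants in a 1:1:1 ratio to the three study arms".

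For the primary outcome, Data Analysis states: "Multinomial logistic regression analysis will be used to compare the likelihood of falling above, within, or below guidelines". The model is fitted after "adjusting for potential confounders such as age, race, ethnicity, socioeconomic status, and household characteristics". The list is open, since its members are given as examples.

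Two routes to the covariates follow in one sentence: "Confounders will be identified through significant findings in bivariate analysis comparing the three groups" "and by consideration of variables based on prior scientific evidence". The article gives no significance level for the first route and no rule for combining the two.

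The same selection is carried to other models. For the weekly weight-gain model: "Additional covariates and effect modifiers included in these regression models will be chosen using the same methods as before". For the Healthy Eating Index (HEI) model: "Models will be adjusted for additional confounders and covariates, determined as in prior models". The complications model is described as analogous to the primary analysis, so it inherits the rule by implication.

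**The concern.** Testing groups for differences in background variables is a habit from observational work, where group membership may depend on those variables. Here allocation is random, so the null hypothesis of such a test is true by design for every baseline variable. A significant result shows only that chance produced an imbalance. What makes a covariate worth adjusting for is its relation to the outcome, and a test of covariate against arm never looks at the outcome.

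Two things are at stake. First, the primary model, and with it the meaning of its conditional odds ratios, depends on which imbalances arise and is known only after the data have been compared by arm. Secondly, a real predictor that is left to this route will nearly always be omitted, and the precision that adjustment for it would bring is lost.

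**Working it through.** **Inputs from the protocol article**
- Sample Size Determination: anticipated proportions within guidelines of 30%, 45% and 60%; 258 per arm after attrition; over 80% power, two-tailed; and "a conservative alpha value of .01 was set for significance to address the multiple testing of 3 comparisons".
- Randomization: three arms, 1:1:1.

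**Assumptions not in the article**
- A selection level of .05, with .01 shown as an alternative.
- 5 to 10 independent candidate covariates. About 5 are named as examples.
- Predictor strength of 0.6 to 1.2 log-odds per SD.

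**Step 1. Reproduce the plan's own figure.** For two proportions with pooled variance under the null and no continuity correction, n = [z(α/2)·√(2p̄q̄) + z(β)·√(p1q1 + p2q2)]² / (p1 − p2)², where p̄ is the mean of p1 and p2, and q = 1 − p. For 45% v 60% at two-sided .01 and 80% power:

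[2.576·√(2 × 0.525 × 0.475) + 0.842·√(0.2475 + 0.24)]² / 0.15² ≈ (1.819 + 0.588)² / 0.0225 ≈ 257.4, so 258.

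This matches the stated 258 (power 0.801). The 30% v 45% comparison needs 242 (power 0.830 at 258). The planned sample size rests on unadjusted proportions and is not in dispute.

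**Step 2. How often the testing route selects.** For a baseline variable under randomisation, the chance of a significant difference equals the test level, whatever the variable's relation to weight gain. In simulation with 258 per arm, analysis of variance across the three arms at .05 selected a strong true predictor in 4.2% to 5.4% of trials. It was therefore missed in about 95%.

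The chance that at least one of k independent candidates is selected is 1 − (1 − level)^k:

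| k | level .05 | level .01 |
|---|---|---|
| 5 | 1 − 0.95^5 = 0.226 | 1 − 0.99^5 = 0.049 |
| 10 | 1 − 0.95^10 = 0.401 | 1 − 0.99^10 = 0.096 |

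The expected number selected at .05 is 0.05 × 5 = 0.25 and 0.05 × 10 = 0.5.

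**Step 3. Power for a predictor left to the testing route.** The simulation used 258 per arm, marginal rates of 45% v 60%, alpha .01, one normally distributed baseline predictor, a logistic model for within guidelines or not, and 4,000 replicates:

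| log-odds per SD | adjust only if p < .05 across arms | always adjust |
|---|---|---|
| 0.6 | 80% | 84% |
| 0.9 | 79% | 87% |
| 1.2 | 81% | 91% |

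A second simulation compared arm 2 with arm 1, with 30%, 45% and 60% set at the predictor's mean. This shrinks the marginal differences and lowers all the power values. It gave 0.70 under the rule v 0.76 with fixed adjustment at log-odds 0.8, and 0.61 v 0.72 at 1.2. The direction is the same.

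**Step 4. Type I error at nominal .01.** In the second simulation (10,000 replicates under the null), the rule rejected at .008 to .009 and fixed adjustment at .009 to .011. The Monte Carlo standard error is √(0.01 × 0.99 / 10,000) ≈ .001. The rule is at most slightly conservative.

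**The case against.** The strongest reply is that the testing route is only half of the sentence. Prior scientific evidence is the other half, and the preceding sentence names plausible candidates. A known predictor can enter that way whatever its p-value, and for that predictor the power gap in Step 3 is zero. This stands. A reader might infer that the planned model will almost never adjust for the real predictors of weight gain. That is true of the testing route alone, not of the model as planned.

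Three further replies also stand:
- A reader might infer inflated false positives. Selection ignores the outcome, so it is not a search for a favourable treatment effect, and the simulations show no inflation.
- A reader might infer that the rule gives each outcome model a different covariate set. With the same candidates and participants, a test of covariate against arm selects the same variables whatever the outcome. The article also describes one method reused throughout.
- A final covariate list may sit in an analysis plan that is not shown, so its absence from the article is no finding.

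None of this rescues the testing route. The article does not leave the matter open: it prescribes a selection criterion that is uninformative in a randomised trial. The second route does not cancel the first, because a variable that tests significant still counts as a confounder.

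**Conclusion.** The point holds in a limited form. One of the two routes to the covariate set is uninformative about prognosis, and it makes the adjusted primary model depend on data compared by arm. The weekly, HEI and, by analogy, complications models share the fault.

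The figures of about 5% per variable and 23% to 40% for at least one of 5 to 10 rest on an assumed .05 level and on independent candidates. At .01 they fall to 1% and about 5% to 10%. They apply to baseline variables only. A measure taken after randomisation and changed by the intervention would be selected more often, which is a separate problem.

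The power difference, roughly 80% against 84% to 91%, is an illustration for a single predictor that enters by no other route. Its true size cannot be derived, because the documents do not give predictor strength. The stated 258 per arm is unaffected, and the randomised, intention-to-treat comparison remains valid.

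**What to change.** In Data Analysis, delete significant between-arm differences as a criterion for choosing covariates. Keep the prior-evidence route and use it to fix one set of baseline prognostic covariates before any data are compared by arm. Candidates could be prepregnancy BMI category, gestational age at enrolment, age, socioeconomic status and food insecurity. Apply the set to all arm comparisons: total gain, weekly gain, HEI and complications. The cross-references in the weekly and HEI paragraphs should then point to this fixed set.

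The cost is a change of wording and slightly less flexibility for the analysts. The sample size and data collection do not change. Adding county terms, leaving p-values out of the baseline table and reporting an unadjusted sensitivity analysis are optional preferences and are not needed to resolve this point.

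### The primary model takes covariates from time-dependent measures without limiting them to values before randomisation, so it may adjust for consequences of allocation

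*Protocol article*

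**What the plan says.** All references are to the protocol article.

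- **Primary model (Data Analysis).** Multinomial logistic regression compares the weight-gain categories "across arms after adjusting for potential confounders such as age, race, ethnicity, socioeconomic status, and household characteristics". The section then adds a second group of covariates: "Summary statistics of key time-dependent measures", together with other, non-time-dependent measures, "measures will also be included as covariates". No time window is set for either group.
- **Choice of covariates (Data Analysis).** "Confounders will be identified through significant findings in bivariate analysis comparing the three groups", and also from prior evidence.
- **Other models (Data Analysis).** The weekly trajectory and Healthy Eating Index (HEI) models choose covariates as the primary model does. The complication models are described as analogous to it.
- **Principle (Data Analysis).** "All analyses will follow the intention-to-treat principle".
- **Table 1, Confounders/modifiers.** The block includes physical activity, collected weekly in pregnancy, and "WIC nutrition visits and food benefits redeemed", taken from WIC records postpartum. Food behaviours and body-shape preference are collected both at enrolment and postpartum.
- **Physical Activity.** The weekly survey yields the share of time in which guidelines are met, collected "as physical activity impacts weight gain in pregnancy".
- **Randomization.** Arms are assigned only after baseline data are in.

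**The concern.** Randomisation makes the arms comparable on everything that precedes it. A variable observed afterwards may have been changed by the arm, and adjusting for it is then no longer confounder control. Two things can go wrong.

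- If the variable lies on the path from delivery to weight gain, adjustment removes part of the effect that the trial is meant to measure.
- If it responds to the arm and shares unmeasured causes with weight gain, adjustment creates an arm difference that allocation did not cause, in either direction.

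The aim, the hypotheses and the sample size all concern the effect of being allocated to delivery. A primary coefficient that conditions on consequences of allocation answers a different question. Because the other models inherit the covariate rule, the weakness extends to the secondary outcomes.

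**Working it through.** **1. Timing.** Assignment follows baseline collection (Randomization). Weekly physical activity and postpartum WIC record data are therefore post-randomisation. Physical activity is the clearest candidate: it is listed as a confounder or modifier, is measured repeatedly, and has a natural summary statistic. WIC visits and redemption qualify by data source and timing.

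**2. Can the arm affect them?** The cost analysis (Data Analysis) counts increased redemption of WIC benefits among the costs of delivering the intervention, so the authors expect redemption to respond, at least in roll-out. For physical activity the article gives no such reason.

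**3. Selection rule.** Suppose a post-randomisation measure is shifted by d SD in both delivery arms (d is assumed), with 258 per arm and a one-way ANOVA at .05 (also assumed, since the article gives no test or threshold). The noncentrality is 258 × d² × 2/3.
- d = 0.2: 6.88, so the measure is selected about 65% of the time.
- d = 0.3: 15.48, so it is selected about 95% of the time.

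Applied to such measures, the rule favours those that the intervention changed.

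**4. What adjustment does.** In a linear model, exactly:

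adjusted difference = unadjusted difference − (arm shift in covariate) × (within-arm slope of outcome on covariate).

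If the slope is causal, the subtracted term is a real part of the effect. If it comes from a shared cause, the term is spurious and can take either sign. If the shift is zero, nothing is subtracted. The logistic model is not exactly linear, but the logic is the same.

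**5. The plan's own figure.** Inputs from Sample Size Determination: 45% versus 60%, two-sided alpha .01, 80% power. With mean proportion 0.525:

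n = [2.576 × √(2 × 0.525 × 0.475) + 0.842 × √(0.45 × 0.55 + 0.60 × 0.40)]² / 0.15² = 257.4, so 258 per arm.

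This matches the stated 258. Power at 258 is 80.1% for 45% versus 60%, and 83.0% for 30% versus 45%. The calculation is for the total, unadjusted difference between arms.

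**6. Illustration.** Let an assumed share s of the 15-point effect run through the covariate. The remaining difference is 15 × (1 − s). Power at 258 per arm, alpha .01, same formula:

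| Share s (assumed) | Remaining difference | Power, from 45% | Power, from 30% |
|---|---|---|---|
| 0 | 15 points | 80% | 83% |
| 25% | 11.25 points | 49% | 54% |
| 50% | 7.5 points | 19% | 22% |
| 75% | 3.75 points | 4% | 5% |

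A simulation agrees (1,500 replicates per share, control rate 30%, linear probability model, covariate shifted by an assumed 0.5 SD). Adjusted differences were 15.1, 11.3, 7.4 and 3.5 points, with power 81%, 51%, 21% and 4%. The unadjusted difference was 15.0, 15.0, 14.9 and 14.0 points. The last value is lower because predicted probabilities were truncated at 1% and 99%. The simulation does not include the shared-cause bias.

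**The case against.** The strongest reply is that the Data Analysis section never names the time-dependent measures. The confounders that it does name are enrolment characteristics. Table 1's heading covers modifiers as well as confounders, so a listed variable need not enter the primary model, and a statistical analysis plan that is not shown may settle the list. This stands as a limit on scope. A reader might infer that the protocol explicitly adjusts the primary model for physical activity, WIC visits and redemption; the text supports them only as likely candidates.

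Four other inferences go too far.

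- *Postpartum food behaviours and body-shape preference are covariates.* Both also have enrolment values, and nothing says that the later ones are used.
- *Redemption would fall because the same foods arrive free.* The only direction given is an increase, and the Intervention section says that deliveries are additional to WIC benefits and not meant to replace their use.
- *The interaction terms come from the same list.* The section refers only to key variables. Table 1's heading makes the link plausible but does not state it.
- *Intention to treat is abandoned, or bias is certain.* Participants are still analysed as allocated, and bias arises only if the arm affects a covariate that is used. For physical activity, the best-supported candidate, no mechanism is given.

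None of this cures the sentence. Summaries of time-dependent measures are a firm commitment, nothing confines them to baseline, and no other part of the article corrects it.

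**Conclusion.** The concern holds as a fault in the stated covariate rule. Followed as written, the rule permits the primary model, and the models that inherit it, to condition on consequences of allocation, and selection by arm differences makes this more likely where the intervention works on such a measure. The arm coefficient would then not target the total effect behind the 30%, 45% and 60% assumptions.

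Confidence is high on the wording, and only moderate on which variables would enter and how large the distortion would be. The power losses above depend on invented mediated shares and are not predictions. The stated sample size is not in dispute.

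**What to change.** Reword the covariate sentences in Data Analysis so that:

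1. covariates and effect modifiers in all primary and secondary arm comparisons are limited to prespecified variables measured before randomisation, with enrolment values only for food behaviours and body-shape preference;
2. covariates are not chosen by testing for differences between arms;
3. physical activity during pregnancy, and WIC visits and redemption, move to a separately labelled mediation or process analysis.

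The cost is a wording change in the analysis text, best made before outcome data are examined by arm. It needs no new data, no more participants and no change to the sample size.
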